## Abstract

**Introduction:**

Percutaneous nephrolithotomy (PCNL) is the standard surgical treatment method for large kidney stones. Its aim is to achieve a stone-free status, since any residual fragments (RFs) after PCNL are likely to cause additional morbidity or stone growth. Enhancing intraoperative detectability of RFs could lead to increased stone-free rates and decreased re-intervention rates. Cone beam computed tomography (CBCT) has recently been introduced in urology as a feasible method for intraoperatively imaging RFs. The aim of this trial is to determine the added value of CBCT in percutaneous nephrolithotomy, by measuring differences in stone-related morbidity for patients with procedures in which a CBCT is used versus patients with procedures without the use of CBCT.

**Methods:**

The CAPTURE trial is an investigator-initiated single-center, randomized controlled trial (RCT) in adult patients who have an indication for percutaneous nephrolithotomy. A contemporary percutaneous nephrolithotomy is performed. Once the surgeon is convinced of a stone-free status by means of fluoroscopy and nephroscopy, randomization allocates patients to either the study group in whom an intraoperative CBCT scan is performed or to the control group in whom no intraoperative CBCT scan is performed. The main endpoint is the stone-free status as assessed four weeks postoperatively by low-dose non-contrast abdominal CT, as a standard follow-up procedure. Secondary endpoints include the number of PCNL procedures required and the number of stone-related events (SREs) registered. The total study population will consist of 320 patients that undergo PCNL and are eligible for randomization for an intraoperative CBCT scan.

**Discussion:**

We deem a randomized controlled trial to be the most effective and reliable method to assess the efficacy of CBCT in PCNL. Though some bias may occur due to the impossibility of blinding the urologist at randomization, we estimate that the pragmatic nature of the study, standardized circumstances, and follow-up methods with pre-defined outcome measures will result in a high level of evidence.

**Trial registration:**

Netherlands Trial Register (NTR) NL8168, ABR NL70728.042.19. Registered on 15 October 2019. Prospectively registered.

## Administrative information

Note: the numbers in curly brackets in this protocol refer to SPIRIT checklist item numbers. The order of the items has been modified to group similar items (see http://www.equator-network.org/reporting-guidelines/spirit-2013-statement-defining-standard-protocol-items-for-clinical-trials/).

## Introduction

### Background and rationale {6a}

Urolithiasis is one of the most common urological diseases and its prevalence has increased over the past decades [1, 2]. In the USA, approximately 1 in 11 people are affected by kidney stones [3]. Emergency department visit rates for urolithiasis have increased by over 90% in the period from 1992 to 2009 [4]. This increasing burden of disease aggravates the need for improving treatment methods for urolithiasis.

The main surgical treatment modality for large (> 2 cm in diameter) or complex kidney stones is percutaneous nephrolithotomy (PCNL) [5]. In PCNL, the kidney is punctured from the flank and dilation of this tract allows for percutaneous access to the kidney. Through this direct rigid access method, stone fragments can be fragmented with powerful fragmentation techniques and stone fragments can be evacuated.

The primary goal of PCNL is a complete removal of stone material, since any left residual fragments (RFs) may cause recurrence of initial symptoms [6, 7].

The practice of PCNL has changed and improved significantly over the years, along with the experience of surgeon s[8, 9]. Access tract diameters have decreased, resulting in less kidney trauma and bleeding. Furthermore, stone fragmentation methods, grasping devices, and baskets have been improved.

In terms of diagnostics of urolithiasis, a shift towards the use of computed tomography (CT) is seen, since it is the most reliable diagnostic tool for imaging urinary stones**.** Radiation exposure has been drastically lowered by developing low-dose non-contrast helical CT protocols. A downside of this imaging modality, however, is that standard helical CT scanners cannot be used intraoperatively.

During a standard PCNL, the surgeon has X-ray fluoroscopy, ultrasonography, and nephroscopy at his or her disposal. However, both fluoroscopy and ultrasonography have a low sensitivity for small or soft stone fragments [10] and full inspection of the renal collecting system by means of nephroscopy can be difficult due to the sinuous nature of the renal anatomy or due to vision impairment caused by bleeding. This leads to a false assumption of a stone-free status in approximately 20% of PCNL cases [11]. Increasing the intraoperative detectability of residual stones could be a major advancement towards increasing stone-free rates and could thereby significantly reduce stone-related morbidity.

As CT is the preferred imaging modality for urinary stones, it would be of great value to enable its use intraoperatively. With the emergence of hybrid operating rooms, cone beam computed tomography (CBCT) has made its entry into several fields of medicine. CBCT scanners do not require the patient or radiation source to translate, as a result of their cone-shaped radiation beam as compared to the conventional fan-shaped beam. The scanner makes a rotation of approximately 200 degrees, and from the detected attenuation profiles image reconstructions can be made that can be viewed cross-sectionally and three-dimensionally.

CBCT has recently been introduced in urology. It has been described in PCNL for the use of needle guidance for gaining percutaneous acces s[12, 13] or for the detection of residual stones [14]. A recently published paper describing a study conducted in our center demonstrated the feasibility of CBCT for the detection of residual stones in PCN L[15]. In this study, we included 19 PCNL procedures with an intraoperative CBCT in order to be able to detect RFs. In 9 out of 19 PCNL procedures, additional stone extraction occurred after making the CBCT scan. Stone-free rates in our study were higher (63% versus 47%) on a 4-week follow-up CT as compared to the CBCT scan.

The evidence that is available to date shows that CBCT in PCNL could increase stone-free rates, while imposing an acceptable burden on patients and the health care system, in terms of radiation dose, additional surgery time, and costs [12–15]. However, several limitations apply to the studies that have already been conducted.

First of all, sample sizes of these studies were relatively small and contained a diverse case-mix, thereby weakening the strength of the results. As of our knowledge, no study has yet evaluated the intraoperative use of CBCT in PCNL with a sample size above 20 patients. Second, investigator bias was not avoided, since the surgeon knew beforehand that a CBCT scan would be made in every case. Thereby, the outcomes of the CBCT scans and additional extraction of stone material could have been influenced.

One could argue that this bias could be bypassed by comparing the (long-term) outcomes of patients in which a CBCT scan was made to aid in residual stone detection with a retrospective cohort without the use of the CBCT scanner. However, the PCNL technique and follow-up methods are rapidly evolving, therefore making it impossible to achieve a comparable control cohort. New stone fragmentation methods have entered the market, and follow-up protocols have altered in both intervals and imaging methods for assessment of the stone-free status.

Therefore, we deem the only effective method to analyze the efficacy of CBCT in PCNL to be a prospective randomized study.

### Objectives {7}

The primary objective of this trial is to determine the added value of CBCT in PCNL, by measuring differences in stone-free rates and stone-related morbidity in patients in whom a CBCT scanner is used versus patients in whom this is not the case.

A secondary objective is to determine whether the use of CBCT in PCNL leads to a significant decrease in the total number of procedures needed per stone case as compared to procedures in which no CBCT scanner is used. Furthermore, we will observe the number of stone-related events (SREs) for patients in both groups, in order to assess the benefits for patients from the use of the CBCT scanner during their intervention.

SREs in this study are defined as follows: recurrence of symptoms, urinary tract infections, stone-related hospital admissions, emergency visits, and re-interventions.

### Trial design {8}

This study is a non-blinded, single-center randomized controlled trial comparing the potential benefits of an intraoperative CBCT scan during PCNL against a standard PCNL without the use of CBCT.

## Methods: participants, interventions, and outcomes

### Study setting {9}

We are currently recruiting consecutive patients in the University Medical Center Groningen (UMCG) that will undergo percutaneous nephrolithotomy (PCNL) for kidney stones.

### Eligibility criteria {10}

In order to be eligible to participate in this study, a subject must meet all of the following inclusion criteria:
≥18 years of ageAvailability of a non-contrast abdominal CT scan with presence of kidney stonesConsent by urologist and patient that a PCNL is the appropriate method for stone removalAble and willing to undergo PCNL and 1 year of follow-upCapacity to give informed consent to participate in the trialFluent in Dutch or English language

A potential subject who meets any of the following criteria will be excluded from participation in this study:
Pregnancy

### Drop-out criteria

Some participants may drop-out during study participation. The drop-out criteria for this study are:
Not eligible for randomizationLoss to follow-upWithdrawal of participation by participant

### Who will take informed consent? {26a}

Consent is taken by the urologist-researcher at the out-patient department, who is trained in Good Clinical Practice (GCP). This will occur during the out-patient hospital appointment, at the point when a potential participant is scheduled for PCNL.

### Additional consent provisions for collection and use of participant data and biological specimens {26b}

The consent form asks participants for permission to contact them in the future for possible participation in further research projects and for permission to use the data that will be collected in this trial for future studies. Declining either of these options has no effect on participation in the CAPTURE trial.

## Interventions

### Explanation for the choice of comparators {6b}

The comparator is an intraoperative CBCT scan during PCNL. Justification for this is given in the “Background and rationale {6a}” section.

### Intervention description {11a}

#### Trial arms

The trial consists of two arms: an arm with patients receiving an intraoperative CBCT scan and an arm with patients that do not receive an intraoperative CBCT scan. The surgery procedure and preparation will be equal for both arms. At the end of the procedure, at the point where the urologist would normally finish the procedure if he would not have a CBCT scanner at his disposal, the randomization will be performed intraoperatively through an internet connection with the randomization software. Patients will be randomized in a 1:1 allocation to either the “CBCT scan” or “no CBCT scan” arm.

#### CBCT scanner and protocols

The CBCT scanner in the urological hybrid operating room of our center is an ArtisQ Ceiling DynaCT (Siemens Healthineers). A dedicated workstation performs three-dimensional image reconstruction and image postprocessing. The CT protocol that is used has a radiation exposure time of 6 seconds, with a total of 397 frames and a radiation dose of 0.36 μGy/f. Slice thickness is set at 2 mm, with an increment of 1 mm. As for reconstruction parameters, a “Hounsfield Units (HU) Kernel” is used and image characteristics are set to “Normal.”

#### Follow-up procedure

For all patients, either in the CBCT-arm or non-CBCT-arm, a 4-week follow-up visit will be scheduled with a follow-up CT. At this appointment, several data, such as postoperative complications, patient complaints, stone analysis outcomes, and the outcome of the follow-up CT will be collected and stored in RedCAP. Several options for further follow-up are possible, depending on the outcomes after PCNL.

#### End of trial

The end of participation in the trial for each participant is defined as having completed the 12-month follow-up visit. Patients may or may not have consented to further data collection for prolonged observation. The data that will be collected in this way can be used for subsequent follow-up trials.

### Criteria for discontinuing or modifying allocated interventions {11b}

No special criteria for discontinuing or modifying allocated interventions are present. Participants in the CBCT-arm will receive an intraoperative CBCT scan, whereas participants in the comparison group will undergo the PCNL procedure according to standard care, which is without a CBCT scan.

### Strategies to improve adherence to interventions {11c}

None. Since the intervention occurs intraoperatively and directly after randomization, we expect no non-adherence to interventions.

### Relevant concomitant care permitted or prohibited during the trial {11d}

Standard care for participants in both arms will continue throughout the trial. There are no special restrictions or permissions.

### Provisions for post-trial care {30}

None beyond standard care.

### Outcomes {12}

#### Primary outcome measure

The primary outcome measure is the stone-free status on follow-up CT four weeks postoperatively. The follow-up CT will be examined by an independent radiologist who is unaware of treatment allocation. The stone-free rates will be calculated into mean stone-free percentages per arm.

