### Sample size {14}

In our feasibility study, the absolute increase of stone-free rate was 16%, with an increase in stone-free rates from 47 to 63%. However, average one-step stone-free rates in literature are higher. For instance, Atmoko et al. report a one-step stone-free rate of 62.6% for staghorn stone s[16]. The stone-free rates in our pilot study were low due to difficult cases with a small study population. Therefore, we based our sample size calculation on a difference of 60% to 75%, with a difference of 15% as the desired difference to prove. With a power of 80% and alfa 0.05 the estimated sample size per arm is 152 patients, resulting in a total sample size of 304 patients. With a 5% margin for possible unexpected loss of patient data, this results in an intended sample size of 320 patients. On average, 80–100 PCNL procedures are performed in our center each year. Taking into account that in some procedures no randomization can be performed, we estimate our rate of inclusion at 60–70 patients per year.

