## Analysis

### Statistical methods for primary and secondary outcomes {20a}

All statistical analyses will be performed using the Statistical Package for the Social Sciences for Windows (SPSS, version 23.0). Descriptive statistics will be presented using mean (± SD) for normally distributed variables and median (IQR) in case variables are not normally distributed. Continuous variables will be compared using *t* tests, whereas for categorical variables, a chi-square test or Fisher’s exact test will be used to compare proportions. A comparison of the primary outcome, the stone-free status on follow-up CT four weeks postoperatively, will be performed with a Chi-square test of the means. A Kaplan-Meier survival analysis will be performed for the survival of SREs and survival of re-interventions per treatment arm, with a log-rank test to assess for statistical significance. For all statistical analyses, an alpha of 0.05 will be used.

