## Discussion

This study will be the first randomized trial evaluating the use of CBCT during PCNL. With a design that standardizes and equalizes circumstances for both arms except for the intervention that is to be evaluated, the imposed burden for participants is kept low while maintaining a high level of evidence.

To date, it is unclear whether the use of CBCT during PCNL can genuinely increase stone-free rates and decrease stone-related morbidity. A positive result of the proposed trial could lead to the adaptation of hybrid operating rooms for PCNL on a larger scale. The results will aid in indicating the circumstances in which performing a “hybrid PCNL” will result in a greater chance of a positive outcome.

Several limitations should be noted for this study. First of all, the unblinded urologist performing the procedure could affect the postoperative outcomes, thereby possibly influencing the secondary outcome measures for this trial. The primary outcome, however, the stone-free status on a 4-week postoperative CT scan, is an objective outcome measure that cannot be influenced in this way.

An ethical dilemma that arises with regard to the design of this study, is that with a relatively large sample size and a 1:1 randomization allocation ratio, a substantial number of participants could be deprived of a potentially superior treatment. Considering possible downsides, e.g., high costs, additional procedure duration, and radiation exposure, a study with a high level of evidence is required in order to conclude whether this technique should be either implemented or rejected.

The interim analysis imposes a limitation for this study, since analyzing the data multiple times increases the chance of occurrence of a Type I error. In this study, no alpha adjustments are made besides setting broad termination boundaries including 95% confidence intervals. This was done in order to maintain a reasonable chance of detecting superiority while maintaining a commonly used alpha of 0.05 at the final analysis.

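### The 4-week stone-free outcome does not account for re-intervention before the CT, so the claim that the surgeon cannot influence it holds only for the blinded reading

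*Protocol article*

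**What the plan says.** - **Outcome.** Primary outcome measure: "The primary outcome measure is the stone-free status on follow-up CT four weeks postoperatively". The CT is read by an independent radiologist who does not know the arm. The section does not mention procedures done before the CT.
- **Care in the interval.** Section {11d} continues standard care in both arms and adds: "There are no special restrictions or permissions".
- **Analysis set.** Section {20c} specifies intention-to-treat.
- **Knowledge at the end of surgery.** According to the Abstract and Trial arms, randomisation takes place when the surgeon would otherwise finish, convinced that the kidney is clear. Section {17a} says the operating urologist performs and interprets the CBCT.
- **Sample size {14}.** The planned rates are chosen after the remark that "average one-step stone-free rates in literature are higher"; then "we based our sample size calculation on a difference of 60% to 75"%.
- **Discussion.** It concedes that the unblinded urologist might affect secondary outcomes, but says the 4-week CT status "is an objective outcome measure that cannot be influenced in this way".
- **Re-interventions.** The number of re-interventions and the time to them are secondary outcomes over 12 months. Time to re-intervention is compared by Kaplan-Meier and log-rank.

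**The concern.** A blinded reader protects the interpretation of the image. He or she does not control what was done to the kidney before the image was taken.

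In the control arm, the surgeon ends the operation believing the patient stone-free and gets no further imaging at that point. In the CBCT arm, the surgeon may see fragments that are not removed in the same session. That knowledge could lead to a second procedure before week 4. If it does, a patient cleared by the second procedure scores as a success, while a control patient with the same fragments, not yet discovered, scores as a failure.

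The primary comparison could then mix two effects: CBCT making the randomised PCNL more complete, and CBCT bringing a second procedure forward. The second is a re-intervention, which the Objectives count as a stone-related event. The same procedure could count against CBCT in a secondary outcome and for it in the primary one.

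**Working it through.** **1. Reproduce the plan's figure.** The plan says: "With a power of 80% and alfa 0.05 the estimated sample size per arm is 152 patients". Inputs are p1 = 0.60, p2 = 0.75, power 80% and alpha 0.05. Sidedness is not stated and is taken as two-sided; a one-sided test would need only 120 per arm. With pooled mean rate 0.675:

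n = [1.960·√(2·0.675·0.325) + 0.842·√(0.60·0.40 + 0.75·0.25)]² / 0.15²
= (1.298 + 0.550)² / 0.0225 ≈ 151.9, so 152 per arm.

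The total is 304, and 304 / 0.95 = 320. The sample-size arithmetic is sound.

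**2. Model the shift.** Let p be the stone-free rate after the randomised PCNL alone, equal in both arms (no true benefit). Let f be the share of CBCT-arm patients with fragments who are re-treated before the CT, and s the share of those who are cleared. No control patient is re-treated early. Then:

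shift = (1 − p)·f·s.

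The documents give neither f nor s. Both are assumptions: f from 5% to 20%, s of 60% or 100%. For p, two values are anchored in the text: 60%, the planned control rate, and 80%, from the Background's figure of about 20% of cases wrongly believed stone-free.

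**3. Chance of a significant result favouring CBCT.** At 152 per arm, with d the shift and m the mean of the two rates p1 and p2:

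Φ{[d·√152 − 1.960·√(2m(1−m))] / √(p1(1−p1) + p2(1−p2))}.

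Example, p = 60%, f = 20%, s = 100%: d = 0.40·0.20 = 0.08, and (0.986 − 1.330) / 0.676 = −0.509, giving 30.5%.

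| p | f | shift, s = 100% | chance | shift, s = 60% | chance |
|---|---|---|---|---|---|
| 60% | 5% | 2.0 points | 5.4% | 1.2 points | 4.0% |
| 60% | 10% | 4.0 points | 10.7% | 2.4 points | 6.3% |
| 60% | 20% | 8.0 points | 30.5% | 4.8 points | 13.6% |
| 80% | 5% | 1.0 point | 4.1% | 0.6 points | 3.4% |
| 80% | 10% | 2.0 points | 6.5% | 1.2 points | 4.5% |
| 80% | 20% | 4.0 points | 14.6% | 2.4 points | 7.7% |

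The nominal chance in that direction is 2.5%.

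**4. In patients.** At p = 60%, 152·0.40 ≈ 61 CBCT-arm patients have fragments. Values of f from 5% to 20% correspond to about 3 to 12 early second procedures in that arm.

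**5. Effect of a re-intervention rule on sample size.** If earlier re-intervention counts as not stone-free and 60% versus 75% is kept as the planning assumption, 152, 304 and 320 are unchanged.

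**The case against.** The strongest reply is that no section describes a second procedure before week 4. The Follow-up procedure section schedules the CT and visit for everyone and then says that later options depend on the outcome, which suggests that further treatment is decided at or after that visit. CBCT-prompted removal is described only within the same session. This stands: the route is open, but nothing shows how often it is used, if at all.

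Several stronger readings are tempting but not supported:

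- **That the pilot sizes the effect.** About 37% of the 19 pilot procedures were not stone-free at the 4-week CT. That is not the share with fragments seen on CBCT and left behind, and the protocol itself calls those cases difficult.
- **That the trial is powered on a one-step rate.** The term describes the literature rates used as context. The 60% and 75% are not so labelled.
- **That re-interventions are hidden.** They are secondary outcomes, and time to re-intervention is compared by arm. What is lacking is a link to the primary result.
- **That only CBCT-arm fragments can be known before the CT.** Control patients may come to light through symptoms or emergency visits. The asymmetry is certain only at the end of surgery.

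Two further objections have weight. In a trial described as pragmatic and analysed by intention-to-treat, earlier clearance prompted by the scan can be seen as a real consequence of CBCT rather than an artefact; the protocol does not say which effect it wants. And counting re-intervention as failure ties the outcome to an unblinded decision: a fragment that would have passed by week 4 is a success in a control patient, but a failure in a CBCT patient re-treated because it was seen.

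Handling of events before the assessment may also sit in an analysis plan not shown here. That does not rescue the Discussion sentence, which is in this document and is too broad.

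**Conclusion.** The point holds in limited form. As written, with no clause on earlier procedures, unrestricted care and intention-to-treat, the primary outcome scores the 4-week CT whatever was done before it. This is inferred from those three provisions together, not from an explicit sentence. Because knowledge of residual fragments at the end of surgery can arise in one arm only, an early second procedure could favour CBCT. The Discussion's assurance is therefore right for the reading of the CT and wrong for treatment before it.

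The size is an assumption. With equal 60% rates after the randomised PCNL, no early re-treatment of controls and all re-treated patients cleared, re-treating 5% to 20% of CBCT-arm patients with fragments gives 2 to 8 points. Incomplete clearance or fewer patients with fragments makes it smaller, and it is nil if no one is re-treated before the CT. A reader might infer that the primary result will be biased, or that the planned 15 points could arise this way. The latter would need 37.5% re-treated and cleared (0.40·0.375 = 0.15), and nothing in the documents suggests such a frequency.

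**What to change.** 1. In {12}, state that the primary outcome is meant to reflect clearance by the randomised PCNL.
2. Pre-specify a key sensitivity analysis in which any stone re-intervention between the randomised PCNL and the 4-week CT counts as not stone-free. If the sponsor intends a one-step rate, make this the primary definition and report plain CT status as the sensitivity analysis.
3. Report the number of re-interventions before the CT by arm, next to the primary result.
4. Limit the Discussion sentence to the reading of the CT.

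The cost is a few sentences and one extra analysis. Re-interventions and the time to them are already collected for the secondary outcomes. Stone-free rates will be slightly lower under the stricter definition, which also depends on an unblinded decision to re-treat; that is why a sensitivity analysis is the safer default. These changes concern how the outcome is counted and reported. They propose no clinical rule on whether or when to re-intervene.
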